#### Strategies to achieve the target sample size

In order to achieve adequate participant enrolment, different strategies are applied: extension of recruiting HCPs (additional inclusion of child and adolescent psychiatrists, direct recruitment via telephone, events, websites), supporting HCPs in enrolment by advertising in different contexts (events, magazines, posters in waiting rooms addressing caregivers directly).

### Statistical analysis

The primary analysis is derived from the intention-to-treat principle, i.e. all randomized patients are analyzed according to their assigned arm, irrespective of whether they refused or dropped out of this treatment or whether other protocol violations occurred.

Linear mixed models for repeated measures (MMRMs) with the fixed effects baseline, group, time, group*time as well as age, sex and symptom severity (at baseline) are fitted (with heterogeneous first-order autoregressive (ARH1) structured variance-covariance matrix over time). The intervention groups are compared by contrasts of marginal means, where the familywise (type I) error is controlled by sequentially conditional rejection (i.e. closed testing). Only patients without valid baseline values are excluded from this analysis. Cluster effects (due to practice, health care provider - HCP) are explored. The influence of missing values is investigated by multiple imputation, particularly those representing missing-not-at-random (MNAR) patterns, where imputation datasets are post-processed by multiplication with factors and addition of offsets (tipping point analysis). The analysis of the participants observed and treated essentially according to the examination plan (per protocol set) is secondary.

The WASH+SUPPORT group and the ESCA-school control group are made comparable to each other (quasi-randomization) by the use of propensity score methods (e.g. by considering age, gender and symptom severity) and differences are analyzed accordingly. The outcome measures of the two studies coincide (symptoms, functional impairment and quality of life).

The moderator analyses refer to characteristics of the parents (e.g. level of education, socioeconomic status, age, psychological stress), characteristics of the family (e.g. family burden, family status) and characteristics of the child (e.g. age, gender, severity of ADHD symptoms, comorbid symptoms). As potential mediators for the effect of the ADHD parent training on the symptoms of the child, the intensity of use of the intervention and the change in parenting behavior are investigated.

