### Primary and secondary outcomes

#### Primary outcome – blinded clinician

The primary outcome is the externalizing symptomatology in the blinded clinical assessment on German clinical rating scales for ADHD and ODD/CD (*Diagnose Checklist für Aufmerksamkeitsdefizit−/ Hyperaktivitätsstörungen (DCL-ADHS)* and *Diagnose Checklist für Störungen des Sozialverhaltens (DCL-SSV)* [31] based on a structured telephone parent interview (ILF-EXTERNAL) [32]. The blinding is achieved through a second rating of the electronically recorded telephone interview with caregivers. Blinding includes group allocation (three groups) as well as assessment time point (four assessment time points). The externalizing symptoms include ADHD symptoms (18 items) and symptoms of oppositional defiant disorder and conduct disorder (13 items) according to ICD-10 and DSM-5. The original interview guide (ILF-EXTERNAL) was adjusted to the age group, i.e. items for adolescents over 12 years of age were removed.

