### Planned sample size and power calculations

It is assumed that a sample of *n* = 700 patients will be recruited for the initial screening (T0). Based on previous comparable projects, 70% of those in the initial screening are expected to meet the inclusion criteria (T1), so that about *n* = 495 patients will be included and randomized. In online-based self-help studies [15, 16], effect sizes are in the lower to medium range (mostly 0.30 ≤ d ≤ 0.70). Telephone-assisted self-help for parents on the basis of booklets has been found to have moderate effects (0.33 ≤ d ≤ 0.59) [10]. For a comparison of two active conditions (WASH vs. WASH+SUPPORT), rather low to most moderate effects are expected (d = 0.30). Therefore, in this RCT study, the aim is to randomize *n* = 132 (ANCOVA, α = 0.05 two-sided, β = 0.20, correlation pre-post 0.5, 29) [42] participants per group. To compensate for drop-out and cluster effects, an additional 20%, i.e. *n* = 495 (≈3 * 132 * 120%) are included (intention-to-treat set).

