### Patient registration and randomization

Patients have to be registered through an HCP nationwide. Participants are assigned to one of three conditions (directly after completion of T1 and after providing informed consent) by a 24/7 Internet service (ALEA, FormsVision BV, Abcoude, NL) that considers (i) gender (female/male) (ii) age (6–9 years or 10–12 years), and (iii) regional factor (rural/urban). The result of the randomization (including further instructions) is sent to the family by e-mail. The randomization is carried out by a member of the research project using the Internet service maintained by the Institute of Medical Statistics and Bioinformatics (IMSB), University of Cologne.

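### The primary mixed model omits rural/urban region, one of the three factors used in randomisation; if region is prognostic, the test is mildly conservative

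*Protocol article*

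**What the plan says.** Under Patient registration and randomization, the protocol article says that the internet allocation service "considers (i) gender (female/male) (ii) age (6–9 years or 10–12 years), and (iii) regional factor (rural/urban").

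Under Statistical analysis, it describes mixed models for repeated measures "with the fixed effects baseline, group, time, group*time as well as age, sex and symptom severity (at baseline) are fitted", with a "heterogeneous first-order autoregressive (ARH1) structured variance-covariance matrix over time". Groups are compared by contrasts of marginal means. Region is not in the list, and nothing in the article explains its absence. The list reads as complete: it carries no qualifier marking it as examples, whereas the propensity-score and moderator variables in the same section do.

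Under Primary outcome – blinded clinician: "The primary outcome is the externalizing symptomatology in the blinded clinical assessment on German clinical rating scales for ADHD and ODD/CD". The article does not say which measure the separate baseline symptom severity covariate refers to.

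**The concern.** Stratified or otherwise balanced allocation makes the arms more alike on the balancing factors than chance would. If such a factor predicts outcome, the treatment estimate varies less from trial to trial. A model that leaves the factor out keeps its variance in the residual, so the reported standard error exceeds the true one. Analysing by the factors used in allocation avoids this. Here two of the three are carried into the model and one is not.

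Region could plausibly matter. The Background says that the supply of behavioural treatment in Germany differs markedly by region, and every arm receives usual care, so what a child receives may depend on where the family lives. At stake is a small amount of precision in a trial sized at almost exactly 80% power for its smallest expected effect.

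A lesser matter is the covariate list itself. The primary outcome is a symptom score, so its baseline already measures symptom severity. A second, undefined severity term leaves the model open to more than one reading.

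**Working it through.** **Inputs from the protocol article (Planned sample size and power calculations).** The settings are "ANCOVA, α = 0.05 two-sided, β = 0.20, correlation pre-post 0.5, 29". For the comparison of the two active arms, "rather low to most moderate effects are expected (d = 0.30"). The stated size is 132 per group.

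**Input not in the documents.** q is the share of post-baseline residual variance explained by region. I assume 2 to 5% as the working range and show 0 and 10% as bounds.

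**Step 1: reproduce the plan's figure.** With unit SD and a pre-post correlation of 0.5, the residual variance is 1 − 0.5² = 0.75.
- Normal approximation: n = 2 × (1.960 + 0.842)² × 0.75 / 0.30² = 130.8, so 131 per group.
- Exact noncentral t: 132 per group, power 80.1%.

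The stated 132 reproduces. It uses only the pre-post correlation, so adding region does not change the required size.

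**Step 2: starting point for one two-arm contrast.** SE = √(2 × 0.75 / 132) = 0.1066, and 0.30 / 0.1066 = 2.814. Power by the normal approximation is Φ(2.814 − 1.96) = Φ(0.854) = 80.4%.

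**Step 3: omit region when allocation is balanced on it.**
- Reported SE / true SE = 1/√(1 − q)
- Type I error = 2 × [1 − Φ(1.96/√(1 − q))]
- Power, region omitted = Φ[(2.814 − 1.96)/√(1 − q)]
- Power, region in the model = Φ[2.814/√(1 − q) − 1.96]

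| q (assumed) | SE overstated by | Type I error | Power, omitted | Power, included | Forgone (points) |
|---|---|---|---|---|---|
| 0% | 0% | 0.050 | 80.4% | 80.4% | 0 |
| 2% | 1.0% | 0.048 | 80.6% | 81.1% | 0.5 |
| 5% | 2.6% | 0.044 | 81.0% | 82.3% | 1.3 |
| 10% | 5.4% | 0.039 | 81.6% | 84.3% | 2.7 |

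**Step 4: check by simulation.** The simulation was a two-arm ANCOVA with 132 per arm, allocation balanced within region, 30% of children in one region stratum (assumed) and 6,000 null replicates. At q = 10% with region omitted, the mean reported SE was 0.1067 against an empirical SD of 0.1006, and the null rejection rate was 0.0365. With region included these were 0.1012, 0.1003 and 0.0478. The Monte Carlo standard error of a rejection rate near 0.05 is √(0.05 × 0.95 / 6000) = 0.003, so the simulation agrees with the formula. The power differences come from the formula, because at 4,000 replicates the simulation error in power (√(0.8 × 0.2 / 4000) = 0.6 points) is as large as the smaller differences.

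**Step 5: the second severity term.** A second covariate correlated 0.8 with baseline (assumed) was added at q = 0. The mean SE of the group contrast was 0.1069 with it and 0.1066 without it, and null rejection with it was 0.051. Collinearity inflates the standard errors of the two severity coefficients but not of the randomised contrast. If the two terms were the same variable, software would drop one and the contrast would not change.

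**Limits.** A single post-baseline ANCOVA stands in for one contrast of the repeated-measures model. The article does not say whether allocation uses stratified blocks or minimisation; the direction is the same for both.

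**The case against.** The strongest reply is that nothing shows region to be prognostic. The Background speaks of regional differences in the provision of treatment, and the Risk-benefit section says only that some areas lack it. Neither reports different symptom change in rural and urban children, and the model already conditions on baseline. This stands, and it is why the size is given as conditional on an assumed range. It does not remove the mismatch: the trial chose region as a factor to balance on, and including it costs one degree of freedom even if it turns out to be irrelevant.

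It could also be said that the plan deals with geography by exploring clustering by practice. Practice effects might pick up part of a regional difference, but that work is exploratory and does not alter the stated primary model.

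Three stronger readings are tempting, and the documents support none of them.
- **That the standard errors are wrong because of both features of the covariate list.** Only the missing region can affect the standard error of the contrast, and only towards caution. The extra severity term leaves it essentially unchanged.
- **That baseline severity is certainly entered twice.** The measure is undefined. It could be ADHD severity alone or the caregiver rating, while the primary outcome combines ADHD and ODD/CD symptoms. The description is also not confined to the primary outcome; for quality of life or parenting, the two terms would differ.
- **That a block of children is thrown away**, for example 2 to 5% of 396, or 8 to 20. Each hypothesis compares two arms (264 children), and balanced allocation has already given the estimate its precision. Only the reported standard error is somewhat too large.

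**Conclusion.** The point holds in a limited form. The stated primary model does not match the stated allocation scheme, because region is missing from it without explanation. For an assumed 2 to 5% of residual variance explained by region, the standard error is overstated by 1.0 to 2.6%, type I error is about 0.048 to 0.044, and about 0.5 to 1.3 points of power are forgone. At 10%, outside the working range, the loss reaches 2.7 points. At zero there is no material loss.

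A reader might infer that the trial is underpowered or its inference invalid. Neither follows. On the plan's own inputs, power with region omitted stays at or above 80.4% throughout the range, and the test is never anti-conservative. This is an inexpensive improvement and not a threat to validity. The undefined severity covariate is a minor matter of specification, with no material consequence for the treatment contrast.

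**What to change.** Add region (rural/urban) to the fixed effects of the primary model, alongside sex and age. The variable is already held in the randomisation system, so the cost is one term in the model statement, with no change to sample size or data collection.

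Separately, name the instrument behind the baseline symptom severity covariate. Drop it for any outcome where it equals the baseline term, and keep it where it carries different information, such as for quality of life. This costs one sentence. Both changes should be made before treatment codes are linked to outcomes, so that the covariate set is not open to choice afterwards.

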### Study design

The trial design is described in Fig. 1. The different conditions: web-assisted parent self-help (WASH), WASH plus additional telephone support (WASH+SUPPORT) and treatment as usual (TAU) are compared in a randomized controlled three-arm parallel group design. Approximately *n* = 700 patients are screened for inclusion and exclusion criteria by their HCPs nationwide (T0). If the inclusion criteria are fulfilled within the pre-assessment (T1, *n* = 495), participating families are randomized to one of the three conditions and receive an E-mail with the randomization result as soon as T1 is completed, including the link to the intervention website (WASH and WASH+SUPPORT). Their personal login information is sent separately. If participants have not logged into the website within 5 days, they receive another E-mail, reminding them to use the website and providing the login information again. Participants randomized to the WASH+SUPPORT group are informed about the procedure during an initial telephone call (or E-mail) and receive further telephone assistance (six calls in the first 3 months after completion of T1). An interim assessment (T2) takes place 3 months after the completion of T1, but not before the SUPPORT calls are completed. This makes it possible to record the course of the effects more accurately and to analyze additional effects of the duration of the intervention. The post-assessment (T3, *n* = 396) takes place after a total of 6 months. In all groups, follow-up (T4, *n* = 316) is performed 6 months after completion of the post-assessment. During follow-up (T3 to T4), a health cost diary is completed. Participating caregivers are asked to note every cost (i.e. money, time, additional costs) in a paper-and-pencil protocol. These data are collected during regular telephone calls by research assistants and are transferred into an online survey form.

Additionally, another non-randomized control group of *n* = 80 children aged 6 to 12 years with an ADHD diagnosis is enlisted from a currently running project, ESCA-school [21]. ESCA-school is part of the research network Evidence-based, Stepped Care of ADHD along the life span (ESCA-life) funded by the German Ministry of Education and Research. Participants receive 20 sessions of face-to-face behavior therapy for a period of 6 months. The project has been operating nationwide since January 2016.

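### The primary MMRM ties visits about 3 and then 6 months apart to one ARH(1) correlation; an unstructured matrix needs only two more parameters and removes a possible bias, mainly at T4

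*Protocol article*

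**What the plan says.** The Statistical analysis section of the protocol article specifies linear mixed models for repeated measures "with the fixed effects baseline, group, time, group*time as well as age, sex and symptom severity (at baseline) are fitted", and it fixes the residual covariance: "with heterogeneous first-order autoregressive (ARH1) structured variance-covariance matrix over time". It gives no reason for the choice, no alternative structure and no robust variance.

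The Study design section sets the visits:

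- T2: "An interim assessment (T2) takes place 3 months after the completion of T1, but not before the SUPPORT calls are completed".
- T3: "The post-assessment (T3, *n* = 396) takes place after a total of 6 months".
- T4: "follow-up (T4, *n* = 316) is performed 6 months after completion of the post-assessment".

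Baseline enters as a fixed effect, so the natural reading is that T2, T3 and T4 are the repeated outcomes. The gaps between them are about 3 and 6 months. The first gap can shrink if T2 is delayed until the support calls end, which can happen in one arm only.

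The analysis section also plans multiple imputation with tipping-point analyses. These vary the assumption about missing values, not the covariance of the primary model.

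**The concern.** ARH(1) lets the variance differ by visit but has a single correlation ρ, applied by visit order and not by elapsed time. A gap of about 3 months and one of 6 months therefore share one correlation, and T2–T4 must equal ρ². Correlations usually fall as the gap widens. Stable differences between children also tend to keep the longest-gap correlation above ρ². Neither pattern fits the restriction.

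With complete data this matters little for the contrasts. With drop-out, a likelihood-based model in effect predicts the missing visits from the observed ones through the fitted correlations. If those are wrong and the drop-out depends on observed scores, the predicted values are off. The error reaches the group contrast when the dependence differs between arms. Such a difference is conceivable here, because families know their allocation and one arm has regular calls, but the document gives no evidence of it.

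**Working it through.** **1. The plan's own figures.** Sample size: n per group = 2·((1.960 + 0.842)/0.30)²·(1 − 0.5²) = 130.8, so 131 against the stated 132, using d = 0.30 and the stated inputs ("ANCOVA, α = 0.05 two-sided, β = 0.20, correlation pre-post 0.5"). The total of 495 equals 3·132/0.80, that is 165 per arm if the arms are equal. Planned loss: 1 − 396/495 = 20.0% at T3 and 1 − 316/495 = 36.2% at T4.

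**2. Parameters saved.** For m outcome visits, unstructured needs m(m+1)/2 and ARH(1) needs m+1. With m = 3 that is 6 against 4, so two are saved. If T1 were also an outcome (m = 4), it would be 10 against 5.

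**3. How the restriction acts.** On a unit-variance scale, the regression of T4 on T2 and T3 has coefficients b₂ = (r₂₄ − r₂₃r₃₄)/(1 − r₂₃²) and b₃ = (r₃₄ − r₂₃r₂₄)/(1 − r₂₃²).

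- All correlations 0.60: the true b₂ = b₃ = 0.24/0.64 = 0.375. ARH(1) fits ρ of about 0.60, hence b₂ = 0 and b₃ = 0.60. For a child seen only at T2, it uses 0.36 in place of 0.60.
- Decay of 0.70 per 3 months: the correlations are 0.70, 0.49 and 0.343 at 3, 6 and 9 months, so the true b₂ = 0 and b₃ = 0.49. ARH(1) fits ρ of about 0.61, hence b₃ = 0.61.

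The first case gives past scores too little total weight (0.60 against 0.75), the second too much (0.61 against 0.49). This is why the sign of the bias cannot be known in advance.

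**4. Size of the bias at T4 under ARH(1).** These are REML fits to simulated data with a true effect of 0. Drop-out is logistic in the last score with slope 1 per SD, T2 is complete, and losses are 20% and 36%. The correlations and slopes are assumptions, because the document gives none. Entries are in SD.

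| True correlations T2–T3 / T3–T4 / T2–T4 | Same in both arms | One arm only | Opposite directions |
|---|---|---|---|
| 0.60 / 0.60 / 0.60 | about 0 | −0.04 | −0.08 |
| 0.70 / 0.49 / 0.34 | about 0 | +0.03 | +0.07 |
| 0.70 / 0.50 / 0.45 | about 0 | +0.02 | +0.04 |
| 0.70 / 0.65 / 0.60 | about 0 | −0.01 | −0.03 |

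Most entries come from 300,000 children per arm; the last opposite-direction entry comes from 165 per arm (Monte Carlo error about 0.005). With slope 0.5 in opposite directions, the first three rows become 0.05, 0.04 and 0.02 in absolute size. If 10% are already lost at T2, T4 bias is 0.02–0.03 with one-arm selection and 0.04–0.06 with opposite directions, for exchangeable or time-decay correlations. For correlations of 0.75/0.65/0.60 it is then at most 0.014, and for a true ARH(1) about 0.

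At T3 the bias is at most about 0.03 SD. Unstructured bias is at most 0.007 SD in all large-sample fits.

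Relative to d = 0.30: 0.01/0.30 = 3%, 0.03/0.30 = 10%, 0.04/0.30 = 13% and 0.08/0.30 = 27%.

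**5. False rejections at T4, 165 per arm.** With 10% lost at T2 (1,500 runs), the worst case is 6.5% under ARH(1) against 4.6% unstructured; the other cases run 4.4–6.1% against 4.7–6.1%. With T2 complete, all correlations 0.60 and opposite directions, 9.2% against 5.8% (500 runs). For 0.70/0.50/0.45 with opposite directions, 4.8% against 6.0% (500 runs, Monte Carlo error about 1 percentage point).

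**6. Precision.** With drop-out unrelated to outcome, the T4 model standard errors are 0.131 (ARH(1)) against 0.127 (unstructured) in one correlation scenario, and 0.137 against 0.133 in another. For a time-averaged contrast the order reverses: 0.083 against 0.085, about 2%.

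**The case against.** The strongest reply is that the harm needs unusual conditions, falls mostly on the follow-up visit, and is small elsewhere. Most of that stands.

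A reader might infer several stronger claims that the document does not support:

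- **That the schedule contradicts ARH(1).** Equal correlations over 3 and 6 months are implausible but possible. If ARH(1) happens to be true, there is no bias.
- **That it was chosen to save parameters.** The article states no motive; only the size of the saving can be counted.
- **That losses of 20% and 36% by themselves cause bias.** They do not. With the same outcome-dependent drop-out in both arms, the T4 bias is about zero. These are also planning figures, and nothing in the document points to opposite selection by arm.
- **That unequal spacing costs 0.08 SD, over a quarter of d = 0.30, with false rejections of 9–12%.** Those figures need opposite-direction drop-out with all correlations equal, a truth that would misfit ARH(1) under equal spacing too. The one run that gave 12.0% gave 7.7% for the nearly unbiased unstructured model, so it reads high.
- **That standard errors are seriously wrong.** At T4 the ARH(1) standard errors are slightly too large, which is conservative.

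The article names no primary time point. Its power calculation uses a pre-post correlation, and 3·132 = 396 is the planned T3 number, so the sizing points to T3, where bias is small. Degrees of freedom and a convergence fallback are ordinary content of an analysis plan, so their absence from an article is no fault.

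The core remains. The article does fix ARH(1), the restriction fits the schedule poorly, the planned sensitivity analyses do not test it, and dropping it costs almost nothing.

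**Conclusion.** The point holds as a minor to moderate weakness in the specification of the primary model, mainly affecting T4. Bias requires that drop-out depends on observed scores and does so differently by arm. Under the assumed correlations and slopes, it is then about 0.01–0.04 SD at T4 for selection in one arm and up to about 0.08 SD for opposite directions, the latter being an extreme. At T3 it is at most about 0.03 SD. The direction cannot be predicted, because it depends on correlations the document does not give. The parameter count assumes that baseline is a covariate and T2 to T4 are the outcomes. The lack of a baseline-by-time term has not been quantified and is not part of this conclusion.

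**What to change.** Specify an unstructured covariance over T2, T3 and T4 with Kenward-Roger degrees of freedom for the primary model. Name ARH(1) with a robust (sandwich) standard error as the prespecified fallback, used only if the unstructured fit does not converge. The robust standard error repairs the variance, not the bias, so the fallback should stay a fallback. A baseline-by-time interaction is an optional refinement (two more fixed effects).

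The cost is one line in the analysis plan, two more covariance parameters and a small risk of non-convergence with about 495 children. The change should be made before unblinded outcome data are seen.
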